### Recruitment {15}

A list of pregnant women in the second trimester who speaks English and or Arabic will be requested. Their contact numbers and the total number and percentage of pregnant women registered at WWRC will be identified at the time of recruitment and during the study period.

### Assignment of interventions

#### Sequence generation {16a}

Probability simple random selection will be selected randomly through the Automated Random Number Generator participants. The obstetric team on the delegation list will screen participants to identify those who fulfill inclusion criteria; then, they will be contacted through phone to consent; this step will continue until the calculated sample size is fulfilled. Each potential participant will be contacted a maximum of three times before withdrawing their name from the potential participant list.

The list of participants who consented to participate will be identified (codes only) with their phone number and contacted to arrange the teleconsultations sessions (six-video sessions) at their convenient time.

#### Concealment mechanism {16b}

Random allocation of the participants will be done into the intervention and control groups. Concealment of group allocation will be done to minimize selection bias. Before commencing the first session, one investigator will randomly allocate eligible participants into two groups. Each participant’s contact details will be written on a printed paper and sealed in an envelope marked with either letter A or B.

#### Implementation {16c}

At the implementation level, another investigator will follow-up with the sessions. The investigator will also hand equal numbers of envelopes to each psychologist randomly. Each psychologist will then open the envelope and contact the patient to begin the teleconsultation session. Patients will give their consent verbally over the phone prior to any teleconsultation sessions.

### Assignment of interventions: blinding

#### Who will be blinded {17a}

Blinding will be done for a data analyst to reduce performance and ascertainment bias. Blinding to data entry will be established by providing a unique code to each subject before entering the analysis data.

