#### Phase one: training of psychologists

The investigators will train two psychologists that are English and Arabic speakers on the WHO materials [19]. Consequently, the data collectors will be prepared to undertake the approved research, motivate interviewers, and ensure the good overall quality of data. The training includes both formal classroom training and hands-on experience with telemedicine techniques.

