#### Phase two: screening and enrolling participants

The investigators will follow the Consolidated Standards of Reporting Trials (CONSORT) in displaying steps of recruitments and randomization. The eligible participants will be selected randomly from the registered pregnant women at Women Wellness and Research Centre (WWRC) and will be contacted by phone to inform the study through verbal informed consent.

Randomization (1:1) with an automated online system ensuring that the research team will not affect randomization. Participants will complete all the assessments via telephone interviewing but following a prewet transcript, and therefore, their responses could be affected by the trial team. A cohort of participants will be followed from the time of approval of the study until the end of interventional sessions (T5-session 6), approximately 1 year after the baby is born. Figure 1 summarizes the study flow.

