#### Who will take informed consent? {26a}

The consent will be taken by delegates’ obstetrics and gynecology physicians of the approved representatives from WWRC in the screening phase through the phone. In the data collection phase, the psychologists will take consent at the beginning of the video call prior to the interview.

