#### Plans to promote participant retention and complete follow-up {18b}

For adherence to the intervention, participants in both groups will be contacted by phone every 3 weeks.

For adherence to questionnaires, psychologists will collect the data through interviews, less commonly to have missing data. In case of missing data, study participants will be contacted and reminded about the completion by a psychologist through telephone.

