## Discussion

To our knowledge, this study is the first research to examine the effectiveness of maternal low-intensity psychosocial telemental interventions in preventing perinatal distress in response to COVID-19 in Qatar.

Cumulative evidence showed that individual psychosocial interventions were more effective than group interventions in preventing and treating perinatal depression. Specifically, face-to-face CBT revealed a protective effect (OR 0.64; 95% CI [0.53–0.75]) and a preventive effect (OR 0.39; 95% CI [0.17–0.60], p 0.001) [26]. Therefore, the regional body of research agreed on the beneficial effects of face-to-face psychosocial interventions. However, there is a lack of studies concerning the effect size of the telemental health approach on perinatal mental health an identified gap to be tested.

The results from this study will show whether maternal low-intensity psychosocial telemental interventions is preventive or not and whether it is recommended to be part of the antenatal package delivered to pregnant women during the COVID-19 pandemic.

One of this study’s strengths is at the level of methodology; applying randomization as a strategy could deal with bias and determine the effectiveness of an intervention in a reliable approach [27]. The prospective nature of the design ensures the temporality between variables and preserves the causation effect. Utilizing a probability sampling technique preserves the external validity of the study. Furthermore, several strategies were employed to decrease the measurement bias, which included extensive training, blinding, and selecting reliable screening tools for assessment. Moreover, it will provide valuable insights into the acceptability of telemental interventions among pregnant women in Qatar, but it is not without limitations. The sample size is not big enough, limiting the generalization of results, and loss of follow-up could be a challenge.

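### Blinding the data analyst is credited with reducing performance and ascertainment bias, which it cannot do, while psychologists who know the arm collect all primary outcomes by interview

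*Protocol article*

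**What the plan says.** All references are to the protocol article.

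**Blinding.** The section on who will be blinded {17a} states: "Blinding will be done for a data analyst to reduce performance and ascertainment bias". Its next sentence adds: "Blinding to data entry will be established by providing a unique code to each subject before entering the analysis data". No blinding of participants, psychologists or outcome assessors is described anywhere.

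**Outcome collection.** The retention section {18b} says that "psychologists will collect the data through interviews". The consent section {26a} agrees: "In the data collection phase, the psychologists will take consent at the beginning of the video call prior to the interview". The Outcomes section {12} places assessment of the primary outcomes in VSee video sessions. Those outcomes are the EPDS-10, its anxiety subscale and the seven-item coronavirus phobia scale.

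**Knowledge of allocation.** Under Concealment mechanism {16b}, envelopes carry the letter A or B. Table 1 labels the intervention A and the control group B. Under Implementation {16c}, each psychologist opens the envelope and contacts the woman to start the session.

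**Risk and safeguard.** The account of phase two concedes of participants that "their responses could be affected by the trial team". The same sentence says that interviews follow a prepared script. The Discussion lists among the study's strengths that "several strategies were employed to decrease the measurement bias, which included extensive training, blinding, and selecting reliable screening tools for assessment".

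**The concern.** Performance bias arises while care is delivered, and ascertainment bias arises while outcomes are recorded. Both are complete before an analyst sees any data. The article therefore credits the trial with a protection that its design does not provide.

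This matters because all three primary outcomes are symptom reports spoken to an interviewer who knows the arm. Women in the intervention arm have up to six one-to-one sessions with a therapist, while control women have outcome screening and usual care. A difference in how symptoms are reported or recorded could then pass for a treatment effect. A reader of the results would also have been told that blinding had dealt with measurement bias.

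**Working it through.** **Step 1: when each blinding measure acts, and on what.**

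| Measure described | When it acts | Can it affect delivery of care? | Can it affect the recorded score? |
|---|---|---|---|
| Blinded data analyst | At analysis | No | No |
| Unique code before data entry | After the interview | No | No |

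Neither measure can do what section {17a} or the Discussion claims. Some authors stretch the term ascertainment bias to include analysts. That would not rescue the claim about performance bias, nor protect a score already recorded.

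**Step 2: whether those who collect the outcomes know the arm.**

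1. The envelope letter shows the arm ({16b} with Table 1), and the psychologist opens the envelope ({16c}).
2. The psychologists conduct the interviews ({18b}, {26a}, {18a}).
3. The content of the contacts reveals the arm in any case: therapy sessions in one group ({11a}), outcome screening only in the other (Control group).

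So psychologists who know the arm collect the outcomes. This follows directly from the text.

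**Step 3: whether the therapist is also the interviewer.** No single sentence says so. Two psychologists are trained on the WHO material (phase one), and the intervention rests on the same reference ({11a}). They start the sessions ({16c}) and they collect the data ({18b}). No other assessor is named. The likeliest reading is therefore that the treating psychologist interviews her own patients. This is an inference, and Step 2 does not depend on it.

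**Step 4: illustration of size.** The point disputes no figure in the plan. The only input taken from it is 29 per arm. As a check on that input, with 34% against 70% and a two-sided 5% level:

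- mean proportion = (0.34 + 0.70)/2 = 0.52
- standard error under the null = √(2 × 0.52 × 0.48/29) = 0.1312
- standard error under the alternative = √((0.34 × 0.66 + 0.70 × 0.30)/29) = 0.1224
- power = Φ((0.36 − 1.96 × 0.1312)/0.1224) = Φ(0.84) ≈ 80%, as planned

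Now suppose there is no true effect, but reporting differs between arms by b standard deviations. The value of b is an assumption, because the documents give none. For a two-sample t-test with 2 × 29 − 2 = 56 degrees of freedom and critical value 2.003, the noncentrality is b × √(29/2) = 3.808b. The rejection probability comes from the noncentral t distribution.

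| Assumed shift b (SD) | Noncentrality | Probability of rejection |
|---|---|---|
| 0 | 0 | 5.0% |
| 0.1 | 0.38 | 6.6% |
| 0.2 | 0.76 | 11.6% |
| 0.3 | 1.14 | 20.2% |
| 0.4 | 1.52 | 32.2% |

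A normal approximation gives 6.7%, 11.9% and 20.8% for the shifts of 0.1 to 0.3 SD, which agrees closely. Blinding the analyst changes none of these figures.

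**The case against.** Unblinded delivery is unavoidable in a trial of talking therapy, and the article does not ignore interviewer influence. Interviews are scripted, the scales have fixed items, staff are trained, and data entry is coded. Scripting and fixed items do limit variation between interviewers. They do not remove knowledge of the arm, and the admission that responses could be affected stands in the same sentence as the script. Coded data entry comes too late to help.

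Four stronger readings are tempting, and the documents do not support them.

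- **That each therapist certainly assesses her own patients, in the same contact as the therapy.** This is inferred. The article speaks variously of therapists, psychologists and data collectors. It also puts assessments by telephone in one place and by VSee in another.
- **That every score is biased towards the intervention.** The direction is probable but not established. Trust in a therapist could also lead women to disclose more symptoms. The baseline score at T0 precedes the first intervention session in Table 1, so a therapeutic relationship cannot have affected it.
- **That the trial's false-positive rate is 12% to 20%.** That range depends on an assumed shift and a simple t-test. The article plans a baseline-adjusted mixed model for repeated measures.
- **That changing who records the answers would remove the bias.** Women know whether they are receiving therapy, so their own response bias would remain.

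The article also gives a reason for interviewing, which is to limit missing data: "psychologists will collect the data through interviews, less commonly to have missing data". That is a fair consideration, and the remedy has to respect it.

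**Conclusion.** The point stands. Section {17a} is wrong to say that analyst blinding reduces performance and ascertainment bias, and the Discussion is wrong to count the blinding described as a safeguard against measurement bias. Psychologists who know the arm collect all three self-reported primary outcomes by interview, and no blinded assessor is described. The scores could be biased, probably towards the intervention.

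The size is unknown. The rejection rates of about 12% to 20% show only what an assumed 0.2 to 0.3 SD shift would do to a simple t-test at 29 per arm, and the conclusion does not rest on them. The errors of wording are certain from the text. The dual role of therapist and interviewer is the likeliest reading and no more than that.

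**What to change.** 1. **Correct the wording in {17a} and the Discussion.** State that participants and psychologists are unblinded, and that blinding the analyst protects analysis decisions only. State the limit this places on conclusions from self-reported scores. The cost is a few sentences.

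2. **Reduce the interviewer's part in the scores.** In both arms, have women complete the three scales themselves immediately before the interview part of the video contact. The psychologist should receive the form within that same contact, so that the existing procedure for EPDS item 10 in {18a} still operates as written. This reduces interviewer bias only. Having the two psychologists assess each other's participants would be weaker, because control women receive only screening and women may reveal their arm.

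The change needs no extra staff, and the Trial status section says that recruitment has not begun. The downside is possibly a few more missing items, which the psychologist can limit by checking the form for completeness during the contact.

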#### Procedure for unblinding if needed {17b}

We do not assume that unblinding will be necessary due to the nature of the intervention.

### Data collection and management

#### Plans for assessment and collection of outcomes {18a}

Data will be obtained at different time points using paper-based questionnaires. In the screening phase, the obstetrics and gynecology team will obtain verbal informed consent through the phone.

In the recruitment phase, the trained psychologists will contact participants via phone to book the video interview’s date and time. Psychologists will secure consent before each video conference.

Structured interview was tested for its face, translation, and content validity by expertise (content validity 90%).

If question 10 in the EPDS-10 showed suicidal intentions, the patient would be directed to the emergency department to one of the HMC hospitals or call the hotline to get an urgent referral to assess mental health services staff corporate policies and guidelines.

#### Data management {19}

Data will be entered and analyzed using the Statistical Package for Social Sciences SPSS® V22.0. All electronic and paper-based data will be stored at the Institute of HMC for a maximum period of 10 years and subsequently destroyed.

#### Confidentiality {27}

All patient-related information will be coded to secure patient protection. For trial analyses, validity-checked data will be transferred in the same way to the study statistician in HMC. The identifiable patient information will be password protected. The code identification list linking the subject’s identity should be maintained confidentially and stored separately in a sealed envelope and kept in a locked cabinet along with the study files with limited access. The team should ensure that screening, enrolment, and randomization details are recorded on a screening/enrolment and randomization log.

### Plans for collection, laboratory evaluation, and storage of biological specimens for genetic or molecular analysis in this trial/future use {33}

Not applicable as no biological specimens were collected as part of this trial.

### Statistical methods

#### Statistical methods for primary and secondary outcomes {20a}

Quantitative variables will be described as mean and standard deviations, whereas the frequency with percentages will be calculated for categorical variables. Both the intervention group and control groups will be described in a table with all the characteristics. Chi-square test will be applied to compare percentages of categorical variables. Regression analysis will be carried to stratify data to eliminate potential confounders and effect modifiers. P value 0.05 (two-tailed) was considered for statically significant level.

We will analyze each continuous outcome with a linear mixed-effects regression model to account for the repeated measures over time. We will analyze binary outcomes with a logistic mixed-effects model. Mixed-effects models are the recommended statistical technique for analyzing clinical trials when outcomes are collected at repeated time points. This trial included outcome data at gestation weeks 14 to 40, 3 to 5 weeks postnatal, 2 to 4 months postpartum, 5 to 7 months, and 8 to 10 months postpartum or postnatal available for all participants who will be randomly assigned. The logistic mixed-effects model has the advantage of implicitly accounting for data missing at random. The estimated (adjusted) effect differences from these analyses therefore will be reported. The linear mixed-effects models will include the response variable, timepoint, randomized group, and baseline score as fixed effects. We will model an interaction between time and the randomized group as a fixed effect to estimate treatment effect at all timepoints. Gestational age and postpartum weeks will be included as covariates in the model. We will calculate standardized effect sizes with Cohen’s d.

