**Methods and analysis:**

The clinical trial is randomized in which pregnant women will be assigned equally through block randomization between two arms: (1) a control group and (2) an intervention group. The primary endpoint is the perinatal psychological distress, including perinatal depression, anxiety, and COVID-19 phobia in their third trimester; the secondary, tertiary, fourth, and fifth endpoints will be in the postnatal period (3–5 weeks, 2–4 months, 5–7 months, and 8–10 months). This trial involves pregnant women in their second trimester with no mental health illness history who communicate in English and Arabic and consent to participate. A sample size of 58 (29 participants per arm) is targeted.

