### Outcomes {12}

#### Primary outcomes

The primary outcomes are baseline (T0) scores of perinatal depression, perinatal anxiety, and COVID-19-specific phobia during late pregnancy and during the follow-up up to 10 months postpartum, additionally computing the changes in the scores from the baseline [(T1–T0), (T2–T1), (T3–T2), (T4–T3), and (T5–T4)].

We will evaluate the primary outcomes through video conferencing sessions via VSee video connection based on standard tools.

Edinburgh Postnatal Depression (EPDS-10) will be used to assess perinatal depression. The scale showed to be a reliable screening tool in Qatar [9]. Cumulative evidence demonstrated a pooled sensitivity of 0.80 and a pooled specificity of 0.81 [21].

The anxiety subscale of EPDS-3A will be used to assess perinatal anxiety. It is identified to have acceptable sensitivity and specificity based on a systematic review of perinatal anxiety tools [22].

Corona-specific phobia, a severe fear specific to the emerging virus, will be assessed through the Corona-Specific Phobia questionnaire that consists of a seven-item scale. Answers are based on the five-item Likert-type scale, and it showed internal consistency (*α* = 0.82) with robust psychometric properties. A total score is calculated by adding up each item score (ranging from 7 to 35). The higher the score, the greater the fear of coronavirus-19 [23].

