### Statistical methods {14}

The required sample size was calculated using the sample size calculation OpenEpi® software version 3.01 available online [24]. In testing the null hypothesis at a 95% level of confidence interval (CI), the error rate of 5% with power = 80%. We used the following formula for sample size calculation:
$$ \mathrm{n}1=\left(\mathrm{Z}\upalpha /2+\mathrm{Z}\upbeta \right)2\ast \left(\mathrm{p}1\left(1-\mathrm{p}1\right)+\mathrm{p}2\left(1-\mathrm{p}2\right)\right)/\mathrm{r}\left(\mathrm{p}1-\mathrm{p}2\right)2 $$

and

n2 = r*n1

where:

n1 = number of exposed (intervention group)

n2 = number of unexposed (control group)

Zα/2 = standard normal deviate for the two-tailed test based on alpha level (relates to the confidence interval level) [alpha = 0.05]

Zβ = standard normal deviate for the one-tailed test based on beta-level (relates to the power level) [beta = 0.2]

r = ratio of unexposed to exposed = 1

p1 = proportion of exposed with the outcome: incidence in intervention group: 34% (we used results from two studies that showed and an improvement between 34 and 69% after delivering the interventions to pregnant women) [18, 25].

p2 = proportion of unexposed with the outcome: incidence in the control group: 70% (since no similar studies have been conducted locally; hence, the estimate p1 was set to 70%).

The sample size needed for each group would be 29 pregnant women, and the total would be 58 participants.

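### The abstract and the Outcomes section disagree on which visits are primary, and on either reading three overlapping scales are primary at 0.05 with no stated rule for what rejects the null

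*Protocol article*

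**What the plan says.** **Which visits are primary.** The abstract (Methods and analysis) sets the primary endpoint as psychological distress, made up of depression, anxiety and COVID-19 phobia, in the third trimester. It then says that "the secondary, tertiary, fourth, and fifth endpoints will be in the postnatal period (3–5 weeks, 2–4 months, 5–7 months, and 8–10 months"). The Outcomes {12} section lists the same three scales as primary in late pregnancy "and during the follow-up up to 10 months postpartum". It also lists baseline scores and five successive visit-to-visit changes under the primary heading.

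**Which scales.** Depression is measured by EPDS-10, anxiety by EPDS-3A (the anxiety subscale of the EPDS), and phobia by a separate seven-item scale. All three are primary in both places.

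**Which test.** Statistical methods {20a} states "P value 0.05 (two-tailed) was considered for statically significant level". For the mixed models it says: "We will model an interaction between time and the randomized group as a fixed effect to estimate treatment effect at all timepoints".

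**Which null.** Objectives {7} states one null covering depression, anxiety and phobia together. It does not say whether a difference on one, two or all three rejects it.

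**What the sample size assumes.** Statistical methods {14} uses "the error rate of 5% with power = 80" per cent, for one comparison of two proportions on an outcome that is not named.

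**The concern.** Two definitions of the primary endpoint cannot both be followed. At analysis, a third-trimester difference with nothing afterwards, or a difference at 8–10 months only, could each be called primary or not, depending on which section is cited. The choice also has practical content: the footnote to Table 1 places the third-trimester assessment (T1) at the first intervention session, so the abstract's only primary visit comes when treatment is starting.

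The second part is the missing decision rule. With three primary scales, one threshold and a bundled null, the reader cannot tell what counts as a positive trial. The Discussion says the results will show whether the intervention is preventive and whether it should join the antenatal package. With 58 women, a chance finding on one scale at one visit could be put forward in support of that, while the planned 5% error rate belongs to a single comparison.

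**Working it through.** **1. Reproduce the plan's own figure.** Inputs from Statistical methods {14}: intervention proportion 0.34 ("p1 = proportion of exposed with the outcome: incidence in intervention group: 34" per cent), control proportion 0.70 ("p2 = proportion of unexposed with the outcome: incidence in the control group: 70" per cent), "r = ratio of unexposed to exposed = 1", two-sided 0.05, power 80%.

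- Printed (unpooled) formula: (1.960 + 0.842)² × (0.34×0.66 + 0.70×0.30) / 0.36² = 7.849 × 0.4344 / 0.1296 = 26.3, so 27 per arm.
- Pooled variance, no continuity correction: (1.960×√0.4992 + 0.842×√0.4344)² / 0.1296 = 29.03 per arm.
- Power at 29 per arm by the pooled version: 79.96%.

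The stated 29 per arm is therefore reproduced as one comparison using the whole 5%.

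**2. Count the tests on each reading.**

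- Abstract: 3 scales × 1 visit (T1) = 3.
- Outcomes section: 3 scales × 5 post-baseline visits (T1 to T5) = 15, before counting the change scores.

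**3. Chance of at least one p < 0.05 when there is no effect.** The independence figure is 1 − 0.95^k. For correlated tests, normal test statistics were simulated (200,000 draws per setting). The documents give no correlations, so these are assumed. Between-visit correlation runs from 0 to 0.8, either constant or decaying with distance. EPDS-10 with EPDS-3A runs from 0.3 to 0.8, and phobia with either from 0.3 to 0.7.

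| Reading | Tests | Independent | Correlated, range tried |
|---|---|---|---|
| Abstract (T1 only) | 3 | 1 − 0.95³ = 14.3% | 11–14% |
| Outcomes section (T1–T5) | 15 | 1 − 0.95¹⁵ = 53.7% | about 26–52% |
| Outcomes section, if only 4 visits | 12 | 1 − 0.95¹² = 46.0% | about 23–44% |
| Visit-to-visit changes only | 15 | 53.7% | about 43–45% |

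The four-visit row is there because the Table 1 header as read has no T4 column although its footnote defines T4. That may be an extraction fault.

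In a middle setting (between-visit 0.4–0.6, EPDS-10 with EPDS-3A 0.75, phobia 0.3–0.5) the 15-test figure is about 35–43% and the single-visit figure about 12%. The 26% is not a floor: one common correlation of 0.8 among all 15 tests gives 20%.

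**4. The opposite rule.** If all three scales had to be significant at a single visit, the false-positive rate in that middle setting is about 0.2–0.5%. It can never exceed the 5% of any one test.

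**5. What a plain split of alpha would cost.** For 34% versus 70% at 29 per arm (pooled version):

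- 0.05/3 = 0.0167 per test: power 64.6%; the printed formula then needs 36 per arm instead of 27.
- 0.05/15 = 0.0033 per test: power 41.9%; the printed formula needs 48 per arm.

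**The case against.** **The analysis plan may hold the rule.** The section on missing data {20c} leaves analysis details to a statistical analysis plan that is not shown. A testing order or alpha adjustment could be there, so its absence from this article is not in itself a defect. That stands. It does not cover the conflict between the abstract and the Outcomes section: what the primary endpoint is belongs in the protocol, and the two statements disagree here. Nor could a later split of alpha be reconciled with a sample size that has already spent the full 5%.

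**The threshold and the visit-specific effects are separate statements.** The 0.05 sentence closes a general paragraph on descriptive statistics, chi-square tests and regression. The interaction sentence speaks of estimating effects, and Cohen's d is to be reported. This also stands: the article does not literally prescribe 15 primary tests.

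**A reader might infer that the trial's false-positive rate is 36–43%.** The documents do not support that as a fact. It needs the Outcomes-section reading, assumed correlations, and a rule that any one significant result means the intervention works. No passage gives that rule, and the bundled null in Objectives {7} could equally be read as requiring all three scales, in which case there is no inflation.

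**A reader might also infer that a postnatal EPDS-10 score should be the primary outcome.** Nothing in the documents settles that. The abstract points to the third trimester, and the choice of scale and visit is the investigators'.

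**The power figures are for a binary outcome.** The loss from 80% to 65% is for two proportions, not for a continuous score in a mixed model, whose power cannot be derived from what is given. It illustrates the cost of a split on the plan's own sample-size basis only.

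**Conclusion.** The point holds as a contradiction in the shown text: third trimester only, against every visit to 10 months plus change scores. On either reading there are three primary scales, two of which share items, one stated threshold, and no statement of which result rejects the null.

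The size depends on a rule the article does not give. If any single significant result counts, the false-positive rate is at least about double the nominal 5% under the abstract and roughly five to eleven times it under the Outcomes section, within the correlations tried. If all three scales are required, it stays under 5%. That the answer can move from under 1% to over 50% on unstated choices is the reason to settle them now. It should be corrected before recruitment, which the Trial status section says has not begun.

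**What to change.** Reconcile the abstract, Objectives {7} and Outcomes {12} so that they state the same hierarchy:

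- **Primary hypothesis:** one scale at one stated visit, or one stated average over visits, chosen by the investigators before recruitment and tested at two-sided 0.05. In choosing, they should bear in mind that T1 is described as the first intervention session.
- **Key secondary:** the other two scales, tested in a fixed order after the primary, or with Holm.
- **Everything else:** remaining visit-by-scale contrasts and the change scores reported as estimates with 95% confidence intervals, without significance claims. Baseline scores should be described as baseline, not listed as an outcome.
- **Sample size:** name in Statistical methods {14} the outcome that the 34% versus 70% comparison refers to, and say how it relates to the chosen primary.

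The cost is wording in the protocol and the registration. The primary test keeps the full 5%, so the hierarchy itself takes no power from it and adds no participants. The small downside is that the two other scales can no longer carry a positive primary claim on their own.
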